## Abstract

**Background:**

An Advanced Care Planning (ACP) program of health decisions is the result of a process of reflection and relationship-building between the patient, their relatives and health professionals. It is based on respect for patients’ autonomy, involving them in making decisions about their disease in a way that is shared between the medical team, the patient and their relatives. Up until now, the efficacy of an ACP has not been measured in the existing literature, and therefore it is unknown if these programs reach their goal. The main objective of our study is to evaluate the efficacy of an ACP program for decision-making in patients with advanced heart failure (HF) in comparison to usual follow up and care. This objective will be evaluated by the Patient Activation Measure test, which measures the participation and self-management of the patient in decision-making. Secondary objectives: to evaluate the effect of the program on quality of life, to know if the patients wishes expressed through the ACP program are fulfilled, to measure the impact of the program on patients’ caregivers, to determine the satisfaction of patients included in the program and to evaluate the effect on quality of death.

**Methods:**

Randomized multicentre clinical trial at four hospitals in Madrid. Once they are included in the study, patients’ allocation to groups (control vs intervention) will be made by alternative sampling. ACP will be applied to the intervention group, whereas in the Control Group usual follow-up will be carried out in HF units. All patients will fulfil questionnaires and tests related to the objectives of the study again after a 12-month follow-up period in order to gauge the effect of ACP in patients with advanced HF.

**Discussion:**

The characteristics of patients with advanced HF make them a model for designing ACP programs, given the high prevalence of this disease, the progressive increase in its incidence and it’s clinical characteristics. Until now, the efficacy of this type of program has not been measured, so this Clinical Trial can provide relevant data for future ACP projects.

*Trial registration* ClinicalTrials.gov Identifier: NCT04424680. Registered 9 June 2020. Retrospectively registered, https://clinicaltrials.gov/ct2/show/NCT04424680?term=NCT04424680&draw=2&rank=1.

## Background

The prevalence and incidence of heart failure (HF) has significantly increased in recent years, in part due to population ageing. It has become the leading cause for admission to Spanish hospitals in patients over 65 years, and currently accounts for 3% of all hospital admissions and 2.5% of the cost of healthcare [1]. While reduction of mortality and morbidity have been the primary objectives in most of HF studies, we must not forget that HF, in addition to increasing mortality, involves a drastic reduction in patients’ quality of life and leads to deterioration of their functional capacity. Taking into account that patients with HF are often elderly, the negative impact of HF on patients’ autonomy in healthcare decisions can be understood.

The Spanish legal framework clearly states both patients and healthcare professionals rights and obligations regarding the clinical relationship. Law 41/2002 regulating patient autonomy was enacted in 2002 [2]. In this Law—as well as in subsequent legal norms—it is specified that patients have the right to state their will in advance through Advance Directives [3, 4]. However, Advance Directives (AD) have little impact on clinical practice, not only in Spain but also in many other countries [5–8]. The lack of impact on clinical practice of AD, as well as the common belief that they only concern patients with terminal illnesses, has led to the conclusion that decision making at the end of life must not depend exclusively on these written forms. These decisions should be centered on communication among doctors, patients and relatives during the end-of-life process [9–11], according to a specific procedure named Advanced Care Planning (ACP) of health decisions. ACP is a structured approach that allows patients, relatives and physicians to discuss end-of-life decisions. ACP enables individuals to define goals and preferences for future medical treatment and care, to discuss these goals and preferences with family and health-care providers, and to record and review these preferences if appropriate [12]. There is evidence that ACP interventions can improve patient-related outcomes such as patient satisfaction with care, quality of communication and shared decision-making [13].

ACP programs for decision-making have been carried out in Spain in diseases like chronic kidney disease, [14, 15], but have not yet been applied to HF. Until now there have not been studies to determine if ACP programs are effective and, consequently, if they meet their objectives. Therefore it is our objective to carry out a Randomized Clinical Trial to evaluate the efficacy an ACP program for health decisions in patients with advanced HF. The aim of this article is to present our study protocol.

## Methods

### Design and study population

Randomized multicentre clinical trial at the Fundación Alcorcón Hospital (Madrid), Ramón y Cajal Hospital (Madrid), Princesa Hospital (Madrid) and San Carlos Clinical Hospital (Madrid) in order to evaluate the efficacy of an ACP program for health decisions in patients with advanced HF. The study will include outpatients with HF according to Framingham diagnostic criteria, in advanced stage of the disease (defined as stage C or D of the ACCF/AHA classification) and with full capacity to decide. Table 1 shows inclusion and exclusion criteria. Patients will be included consecutively and followed for one year.

**Table 1 Tab1:** Inclusion and exclusion criteria

*Inclusion criteria*
Patients with HF defined by Framingham diagnostic criteria
Stage C or D of the ACCF/AHA classification
Full capacity to decide
Signing of informed consent
*Exclusion criteria*
Cognitive impairment, measured by Mini-Mental Status Examination (< 27)
Presence of another disease other than HF that may severely affect the quality of life: stroke with significant residual deficit, end-stage renal failure, Child C cirrhosis, extreme obesity, haemoglobin < 8 g/dl, advanced peripheral artery disease (stage III–IV), severe thyroid or adrenal disease, neoplastic with estimated survival of less than 2 years
Patients who do not sign the informed consent

### Objectives

The main objective is to evaluate the efficacy of an ACP program for decision-making in patients with advanced HF in comparison to usual follow up and care. This objective will be evaluated by the PAM (Patient Activation Measure) test, which measures the participation and self-management of the patient in decision making. Secondary objectives are: to evaluate the effect of the ACP program on quality of life, to know if the patients wishes expressed through the ACP program are fulfilled, to measure the impact of the ACP program on patients’ caregivers, to determine the satisfaction of patients included in the program and to evaluate the effect on quality of death. Secondary objectives will be assessed through questionnaires specifically developed for each objective.

### Study procedure

Researchers will attend a training course prior to the commencement of the study and the ACP program, with the aim of learning how to carry out the tests employed in the study. The research staff will prospectively carry out data collection. Candidate patients will be informed orally and in writing about the study prior to signing the informed consent. An informed consent form will be needed to participate in the study. Before being accepted, patients will be required to perform a Mini-Mental Status Test. Those scoring under 27 will be excluded.

Once patients have been included in the study, the assignment process will be carried out by random sampling to the study groups. In the First Group (control group), patients will be followed in HF outpatients units according to the usual established protocol. In the Second Group (intervention group), patients will participate in the ACP program. Treatment for HF will be the same in both groups. The research team has developed the ACP program based on the published bibliography on ACP and advanced HF. The four hospitals mentioned will start recruiting at the beginning of the study. The principal investigator will be responsible for interrupting recruitment once the sample size has been reached (Additional file 1).

In the first visit, patients from both control and intervention groups will complete the following questionnaires with the help of researchers:PAM (Patient Activation Measure) Test (Table 2) [16]: test to measure the activation (participation and self-management) of the patient in decision-making. It evaluates the knowledge, skills and confidence of patients’ self-management classifying patients in levels of self-management activation. It also values the degree of patients’ implication in making decisions about their lives (in their self-management). This procedure has been previously applied to frail elderly patients in a Dutch study in order to measure patients’ activation in decision making. The test divides the patients in four levels according to their decision-making capacity:

**Table 2 Tab2:** The PAM 13 measurement instrument

PAM assesses a consumer’s knowledge, skills and confidence for self-management. PAM segments people into one of four progressively higher levels of activation. Below are some statements that people sometimes make when they talk about their health. Please indicate how much you agree or disagree with each statement as it applies to you personally by circling your answer. Your answers should be what is true for you and not just what you think others want you to say		
1	When all is said and done, I am the person who is responsible for taking care of my health	Disagree strongly Disagree Agree Agree strongly N/A
2	Taking an active role in my own health care is the most important thing that affects my health	Disagree strongly Disagree Agree Agree strongly N/A
3	I am confident I can help prevent or reduce problems associated with my health	Disagree strongly Disagree Agree Agree strongly N/A
4	I know what each of my prescribed medications do	Disagree strongly Disagree Agree Agree strongly N/A
5	I am confident that I can tell whether I need to go to the doctor or whether I can take care of a health problem myself	Disagree strongly Disagree Agree Agree strongly N/A
6	I am confident that I can tell a doctor concerns I have even when he or she does not ask	Disagree strongly Disagree Agree Agree strongly N/A
7	I am confident that I can follow through on medical treatments I may need to do at home	Disagree strongly Disagree Agree Agree strongly N/A
8	I understand my health problems and what causes them	Disagree strongly Disagree Agree Agree strongly N/A
9	I know what treatments are available for my health problems	Disagree strongly Disagree Agree Agree strongly N/A
10	I have been able to maintain (keep up with) lifestyle changes, like eating right or exercising	Disagree strongly Disagree Agree Agree strongly N/A
11	I know how to prevent problems with my health	Disagree strongly Disagree Agree Agree strongly N/A
12	I am confident I can figure out solutions when new problems arise with my health	Disagree strongly Disagree Agree Agree strongly N/A
13	I am confident that I can maintain lifestyle changes, like eating right and exercising, even during times of stress	Disagree strongly Disagree Agree Agree strongly N/A

*Level 1* They do not feel responsible for their own health and care. Health management is overwhelming for them, considering all the problems of life. They lack confidence in their ability to manage health. They have few solving problem skills and poor coping skills. They may not be fully aware of their behaviour (Score 47.0 or lower).*Level 2* They may lack basic understanding about their condition, treatment options, and/or self-care. They have little experience making decisions. They consider their doctor as the decision maker. They have little confidence in their ability to manage their health (47.1–55.1).*Level 3* They know the basic facts of their illness and treatments. They have some experience making decisions and some confidence in the management of certain aspects of their health (55.2–67).*Level 4* They have made most of the decisions, but they may have difficulties in maintaining behaviours over time or in stressful situations (67.1 or higher).MLWHFQ Questionnaire (Minnesota Living with Heart Failure Questionnaire) [17]: validated to analyze the quality of life in patients with HF (Spanish version). Scoring range: 0 to 105 points: The higher the score obtained, the poorer the quality of life of patients. Patients wonder to what extent their illness has prevented them from living the way they wanted last month. Questions refer to signs and symptoms of the disease, social relationships, physical, sexual activity, work and emotions. It is self-administered, with Likert response options, ranging from 0 (quality of life not affected) to 5 (maximum impact on quality of life). The global MLWHFQ score is obtained by adding the 21 items scores (range: 0–105); the highest value corresponds to the worst HRQL. It assesses the impact of chronic heart failure in two dimensions: the physical dimension based on eight items (range: 0–40) and the emotional dimension consisting of five items (range: 0–25).Zarit questionnaire about caregiver's burden [18]. This interview measures caregivers’ degree of subjective overload in relation to chronic patients. It consists of 22 items that collect caregivers’ feelings. Each feeling scores on a frequency gradient that ranges from 1 (never) to 5 (almost always). Interpretation:or < 45 points: no overload47–55 points: slight overloador > 55 points: intense overloadIn addition, the following data will be collected: epidemiological data (date of birth, sex), presence of diabetes mellitus, dyslipidaemia, alcohol and tobacco consume, thyroid disease, etiology of cardiomyopathy, left ventricular ejection fraction, heart devices, Charlson index, hours of weekly physical exercise, sociocultural characteristics (marital status, housing, people living in the house, education, employment status, economic income per year, religion) and also characteristics of the main caregiver (number of caregivers and who is the main caregiver, relationship with the patient, caregiver's employment status).

After 1 year of follow-up, the questionnaires will be submitted again to all patients and three new questionnaires will be proposed:Patient's wishes checklist: Checklist to test the fulfilment of planned patient's wishes. Two parameters (patient participation in the decision-making thought PAM Test and fulfilment of their wishes) allow us to determine whether decision-making in advanced HF is actually being effective.Satisfaction questionnaire (Table 3): Created “ad hoc”, it aims to assess the level of satisfaction with the program. Its outcome will help improve the future implementation of the program.

**Table 3 Tab3:** Satisfaction questionnaire

Answer YES or NO	YES	NO
Did you understand what the program was about?		
Do you feel you received enough information, orally or in writing, for your understanding?		
Did you feel that you could easily access the doctors responsible for the program to answer your questions?		
Do you think that the doctors responsible for the program have the necessary skills and knowledge?		
Did you understand without difficulty what these professionals communicated in each interview?		
Has the program met your expectations and needs?		
Did you find it easy to get to the office and/or day hospital?		Dying and Death quality questionnaire (QODD) [19]: This questionnaire measures the quality of the dying process. It will be submitted to the relatives of patients who passed away during the year of follow-up.The Satisfaction questionnaire has been developed for this study. The other questionnaires had already been previously published.

All data will be registered in a database created for the purpose of the study.

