### Randomization

Subjects’ allocation to the two groups will be carried out by simple random sampling stratified by hospital. This sampling will be processed by a computer program that randomizes the patients in each hospital. Randomization will result in two lists of random numbers between 1 and 50 in each hospital. In each research center there will be 50 opaque and sealed envelopes numbered from 1 to 50. Each envelope will contain the group for that particular patient (intervention vs. control). The number on each envelope will correspond with the entry order number of each subject and will be opened once the patient has been included in the study. Each hospital must recruit a minimum of 20 patients and a maximum of 50 patients. Recruitment will end when sample size is reached.

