### Limitations of the study

Even if the ACP program intervention is homogeneous in both groups, and everyday clinical practice is very similar in all centers, the organization of each HF Unit can vary. Despite this fact, this scenario parallels real clinical variability. Even though clinical management will be similar in both groups, as an open clinical trial there is a risk of expectation and attention bias. This might make it difficult to ensure that researchers' higher engagement with patients in the intervention group will not skew results. Finally, the study is restricted to patients with advanced HF, and therefore its conclusions and extrapolation to other advanced chronic pathologies is limited.

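### As the procedure reads, baseline PAM is completed with researcher help after the arm is known; baseline questionnaires should be required before the envelope is opened

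*Protocol article*

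**What the plan says.** The Objectives section makes the PAM the measure of the main objective: "This objective will be evaluated by the PAM (Patient Activation Measure) test".

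The Study procedure section first has consent and the Mini-Mental test, the latter required before a patient is accepted. It then says: "Once patients have been included in the study, the assignment process will be carried out by random sampling to the study groups". After describing the two groups, it turns to the baseline measurements: "In the first visit, patients from both control and intervention groups will complete the following questionnaires with the help of researchers". The questionnaires listed are PAM, MLWHFQ and Zarit. The same section says of the data generally: "The research staff will prospectively carry out data collection".

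The Randomization section says that the numbered envelope "will be opened once the patient has been included in the study". It does not mention the questionnaires.

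The Limitations section concedes that "as an open clinical trial there is a risk of expectation and attention bias", and adds that researchers' greater engagement with intervention patients could skew results.

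At one year the questionnaires are given to all patients again. The article does not say whether researchers help on that occasion.

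**The concern.** The PAM asks patients how far they agree with statements about their own confidence and knowledge. Answers of this kind can move with what the patient expects and with who is helping. If the envelope has been opened, the patient may already know that the ACP program is coming, or is not, and the researcher helping may know it too. The baseline is then no longer a clean pre-randomisation value, although randomisation is what would make it comparable between arms.

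What is at stake is any analysis that uses baseline PAM, either by subtracting it or by adjusting for it. Such an analysis would treat a shift caused by knowledge of the arm as a pre-existing difference between patients and correct for it wrongly. In addition, a patient who withdraws on learning the arm would leave no baseline record.

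**Working it through.** **1. Order of events**

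| Step | Where stated | Relation to allocation |
|---|---|---|
| Consent, Mini-Mental | Study procedure | Before acceptance, so before assignment |
| Inclusion, then assignment | Study procedure | Assignment follows inclusion |
| Envelope opened | Randomization | Once the patient is included |
| PAM, MLWHFQ, Zarit with researcher help | Study procedure | First visit, patients already described by group |

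The Mini-Mental is the only test expressly placed before assignment. A site following the text could open the envelope first and comply fully.

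**2. The plan's own scale**

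The Sample size section uses a standardized difference of 0.5, 80% power and 95% confidence, and gives 64 per arm (128). With a two-sided 5% t-test (noncentral t), 64 per arm gives power 0.8015 and 63 per arm gives 0.7952. The figure of 128 therefore reproduces, and 0.5 SD is the yardstick below.

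**3. Effect of an arm-dependent shift**

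Let d0 and d12 be the spurious intervention-minus-control shifts in PAM at baseline and at 12 months, in SD units. Let r be the within-arm correlation between the two scores, with equal SDs, so that the regression slope is r. The error in the estimated effect is:

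- 12-month scores only: d12
- change score: d12 − d0
- baseline-adjusted (ANCOVA): d12 − r × d0

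If only baseline is affected (d12 = 0), these become 0, −d0 and −r × d0. A baseline shift that raises PAM in the intervention arm therefore counts against the intervention, and one that lowers it counts in favour.

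The documents give neither d0 nor r. Assuming d0 = 0.1 to 0.2 SD and r = 0.5:

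- change score: error 0.1 to 0.2 SD, which is 0.1/0.5 = 20% to 0.2/0.5 = 40% of the target
- ANCOVA: 0.5 × 0.1 = 0.05 to 0.5 × 0.2 = 0.10 SD, or 10% to 20% of the target

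**4. Chance of a false positive in either direction**

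Settings: 64 per arm, no true effect, two-sided 5% test. The error is divided by √(1 − r²) for ANCOVA and by √(2(1 − r)) for change. Noncentrality is the result times √(64/2).

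Example with r = 0.5 and d0 = 0.2:

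- ANCOVA: 0.10/0.866 = 0.115; 0.115 × 5.657 = 0.65; rejection about 9.9%
- Change: 0.2/1 = 0.2; 0.2 × 5.657 = 1.13; rejection about 20.2%

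| r (assumed) | d0 (assumed) | ANCOVA error, SD | ANCOVA rejection | Change error, SD | Change rejection |
|---|---|---|---|---|---|
| 0.3 | 0.1 | 0.03 | 5.4% | 0.1 | 7.6% |
| 0.3 | 0.2 | 0.06 | 6.4% | 0.2 | 15.8% |
| 0.5 | 0.1 | 0.05 | 6.2% | 0.1 | 8.7% |
| 0.5 | 0.2 | 0.10 | 9.9% | 0.2 | 20.2% |
| 0.7 | 0.1 | 0.07 | 8.5% | 0.1 | 11.2% |
| 0.7 | 0.2 | 0.14 | 19.6% | 0.2 | 30.5% |

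**5. If the same shift occurred at both visits**

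With d12 = d0, the error cancels in a change score and falls to (1 − r) × d0 under ANCOVA, which is 0.05 to 0.10 SD at r = 0.5. It remains in full in a comparison of 12-month scores, where 0.1 or 0.2 SD gives a rejection rate of about 8.7% or 20%. Nothing in the article establishes a 12-month shift; this case only shows that the size and sign of the error depend on when the shift arises.

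**The case against.** The strongest reply is that the order is inferred. No sentence says that PAM follows the opening of the envelope. The Study procedure section is not strictly chronological, since it describes follow-up by group and the end of recruitment before it reaches the first visit. Naming both groups may only mean that everyone completes the same forms. Additional file 1, cited there, was not available. This stands as a limit on certainty. It does not remove the point, because the text as written permits the arm to be known first and nothing stated prevents it.

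The second reply is that a baseline shift matters only if baseline PAM is used. The Statistical analysis section names two-group tests and multiple linear regression, without naming a change score or baseline PAM as a covariate. This also stands.

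A reader might infer more than the article supports:

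- **That 12-month PAM is answered with the same help.** Help is stated for the first visit only.
- **That those who deliver ACP help patients with the PAM.** Data collection is given to research staff, and the satisfaction questionnaire refers to doctors responsible for the program. Nowhere are the two said to be the same people.
- **That the procedure favours the intervention.** A baseline shift towards the intervention works against it in a change-score or adjusted analysis.
- **That the MLWHFQ instructions contradict each other.** "It is self-administered, with Likert response options" describes the instrument's format, and a patient can complete such a form with someone on hand to help.

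Finally, the Limitations section admits expectation and attention bias, and ACP participants cannot be blinded. That is fair for the 12-month answers. It does not bear on baseline, which can be measured before anyone knows the arm.

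**Conclusion.** The point holds as one about the order of procedures. On the natural reading of Study procedure and Randomization, allocation is revealed at inclusion and the baseline questionnaires follow, with researcher help, in an open trial. Baseline PAM can therefore be influenced by knowledge of the arm.

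If baseline alone is affected, the distortion is the full shift in a change-score analysis, r times the shift in a baseline-adjusted one, and nil in a comparison of 12-month scores alone. Its direction cannot be assumed. The sizes shown rest on shifts of 0.1 to 0.2 SD and correlations of 0.3 to 0.7, which are assumptions and not estimates from the documents.

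The change is worth making because it protects the baseline of a subjective primary outcome at almost no cost. Confidence is medium, since the order is not fixed outright.

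**What to change.** **Main change.** State in both Study procedure and Randomization that consent, the Mini-Mental and all baseline questionnaires (PAM, MLWHFQ, Zarit) are completed before the envelope is opened. Consent and the Mini-Mental already come first, so only the questionnaires need to be placed. If that is already the intention, the same sentence removes the ambiguity.

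**Secondary safeguard.** Since the 12-month mode of completion is not stated, have PAM and MLWHFQ self-completed at that visit where possible. Where a patient needs help reading, an existing team member who did not deliver ACP to that patient reads the items verbatim. Such a helper may still know the arm, so this reduces the risk of influence but does not mask the assessment.

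**Cost.** A sentence in each section, a line in the planned researcher training, and some scheduling of who assists at 12 months. No extra visit is needed, and the sample size of 128 (140 with the allowance for losses) is unchanged.
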